### Inclusion criteria

Eligible patients for the proposed trial are pregnant women recognized to be at risk of adverse pregnancy outcome associated with FGR at mid gestation. Since poor placental function and mal-perfusion of the placenta is recognized to cause FGR [3] impaired placental flow measurement is strongly associated with the development of FGR. A mean pulsatility index >95th percentile according to Cnossen et al. predicts FGR with a sensitivity of 18% with a specificity of 95% in a general population and a sensitivity of 58% for any FGR in a high risk population with a specificity of 75% [4]. The risk to develop FGR is in general higher in women with a medical history of chronic hypertension, diabetes mellitus type 2, systemic lupus erythematodes or antiphopholipid antibody syndrome and in those with prior history of adverse pregnancy outcome associated with FGR (late pregnancy loss, stillbirth, abruption placentae, preterm delivery, preeclampsia or HELLP-syndrome) [13]. Accordingly, at least one third of the pregnant women diagnosed with impaired perfusion of the uterine arteries at mid gestation will develop FGR and associated adverse pregnancy outcomes. In the presence of additional risk factors this likelihood will rise considerably.

Consequently, the Inclusion criteria are impaired uterine artery Doppler ultrasound, defined by a mean Pulsatility Index (PI) greater than 1.6 (> 95th centile of German reference population, PIA Fetal Database, Version 4.00 and higher, Viewpoint, Germany; [14]), singleton pregnancy at 19^0^ to 22^6^ weeks of gestation who are over 18 years old and provide informed consent.

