### Primary outcome measures

As primary efficacy endpoint development of FGR (< birth weight below the 10th centile) or perinatal death as a composite outcome was proposed in accordance to the pilot study [12]. Key secondary endpoints are severe morbidity and mortality as composite of severe FGR, intrauterine or neonatal death or placental abruption, birth weight below the 3rd, 5th and 10th centile according to Voigt [15], development of FGR requiring delivery before 30 and before 34 weeks` gestation, spontaneous preterm delivery before 34 weeks and before 37 weeks gestation, rate of neonatal intensive care unit admission and neonatal complications like the need of ventilation, occurrence of intraventricular hemorrhage II – IV ° or necrotized enterocolitis.

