### Experimental and control interventions

Following randomisation, oral intake of PETN or placebo two times daily will be continued until 36^6^ weeks. Maternal and fetal status and condition will be assessed every 4 weeks during the treatment period and at 38^6^ to 40^0^ weeks. (Table 1) Outcome data will be collected after delivery for neonatal (weight, height, APGAR 1′/5′/10′, umbilical artery pH, gestational age at birth, admission to the neonatal intensive care unit, respiratory distress syndrome grade III or IV, occurrence of intraventricular haemorrhage grade III or IV or parenchymal bleeding or periventricular leukomalacia, necrotized enterocolitis, neonatal death) and maternal pregnancy associated morbidity. Additionally, data on child development will be documented on growth, health status and intellectual development at the age of 12 months, by collecting the routine check-up data from the paediatricians. (Table 1).

**Table 1 Tab1:** Study procedures

Study Period	Recruitment period	Treatment period (12–19 weeks) Study visits fourweekly				Post-Treatment-Follow-up		
Treatment	start at inclusion	oral intake of 50 mg PETN/Placebo 2 times daily				Follow up		Follow up child
Event/Visit	Inclusion visit at 19^0^ to 22^6^ weeks	24^0^ to 24^6^ weeks	28^0^ to 28^6^ weeks	32^0^ to 32^6^ weeks	36^0^ to 36^6^ weeks	38^0^ to 40^0^ weeks	after delivery^h^ (no visit)	Routine check-up at the age of 12 month^i^
Informed Consent	x							
Inclusion/Exclusion Criteria	x							
Randomisation	x							
Ultrasound ^a^	x	x	x	x	x	x		
Maternal status^b^	x	x	x	x	x	x	x (at admission for delivery)	
Haematology/Urinanalysis^c^	x	(x)	x	(x)	x	x	x (if available)	
Maternal condition^d^	x	x	x	x	x	x		
Concomitant medication^e^	x	x	x	x	x	x		
Checking for AEs incl. SAEs		x	x	x	x	x	x	x
Perinatal outcome^f^							x	
Maternal morbidity^g^							x	
Data on child growth and development								x

^a^assessment of fetal growth: head and abdomen circumference, femur length, doppler of aa. aterinae, a. umbilical and a. cerebri media, amniotic fluid index

^b^assessment of maternal status: blood pressure, weight

^c^assessment of haematology and urine: blood count, ASAT, ALAT, LDH, proteinuria and determination of sflt and PlGF amounts and ratio where possible

^d^assessment of maternal condition: head ache, nausea/vomiting, ear or eye symptoms, pain in the upper abdomen, oedema, others

^e^concomitant medication: name, dosage, frequency, duration, reason of intake

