### Statistical analysis

Baseline characteristics of patients will be compared by descriptive statistics to assess the success of randomization. The primary endpoint (binary variable) will be presented by group-specific incidences. The confirmatory test of the treatment effect stratified for risk-groups will be performed by the Mantel-Haenszel test. Mantel-Haenszel estimates of relative risks and their 95% confidence intervals will be calculated. Primarily, data will be analyzed according to the intent-to-treat (ITT) principle. The ITT-population will include all randomized patients with valid primary outcome data who have received at least one dose of study medication (full analysis data set). The drop-out rate is expected to be 10%. Missing values of the primary endpoint are multiply imputed to confirm the robustness of the main results (sensitivity analysis). All secondary endpoints (binary variables) will be analysed by Mantel-Haenszel methods as described above. In a sensitivity analysis generalized mixed linear models with treatment and risk indicator as fixed, and centre as random factor, will be fitted to adjust for variability between study centres. Explorative analyses of endpoints will be additionally performed for subgroups according to time of delivery and maternal age. AEs/SAEs will be listed. Incidence of events and descriptive statistics (quartiles, mean, standard deviation) of laboratory safety data will be displayed in treatment groups. No adjustment for endpoint multiplicity is planned. All tests will be done at a comparison-wise significance level of 0.05.

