## Discussion

FGR is the most important determinant of perinatal outcome in pregnancies with impaired utero-placental perfusion, at worst resulting in perinatal death. The relevance of reducing the occurrence, rate and extent of FGR is obvious in light of the associated outcomes. FGR neonates have an incredible risk to develop neonatal complications and lifelong health effects [2]. A reduction of this burden and the additional decrease in the rates of prematurity and perinatal death will be of tremendous benefit for the affected women. Furthermore, reduction of FGR and prematurity might additionally decrease the long-term consequences like development of diabetes and obesity in the affected children, thereby also contributing to relieve the general health system. The chosen composite endpoint represents the most severe outcome possible in growth restricted pregnancies and is justified by being the endpoint of our pilot study.

The management of FGR so far is driven by an approach to delay delivery, since prematurity is the most important determinant for perinatal outcome and lifelong health in growth restricted newborns. Nevertheless, in cases where intrauterine hypoxia is rising and intrauterine asphyxia and death is threatening, preterm delivery is required to save the baby’s life. Thus, prematurity is often associated with FGR, thereby deteriorating the infants long-term prognosis. The clinical parameters accepted to determine long-term clinical outcome of preterm children are the occurrence and severity of intracerebral bleeding, severe bowel affection (necrotized enterocolitis) and the long-time lung function which is determined by the fetal respiratory distress syndrome [17–19]. Therefore, preterm birth and very early preterm delivery, as well as perinatal outcome data was chosen as secondary endpoints.

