Eligible patients for the proposed trial are pregnant women recognized to be at risk of adverse pregnancy outcome associated with FGR at mid gestation by impaired uterine perfusion. In the absence of a general screening for placentation failure by Doppler measurement at mid gestation in all pregnant women, those recognized with impaired placental perfusion are more likely to present with additional risk factors and do not represent the general population. However, since the effectiveness of PETN to substantially improve pregnancy outcome has been especially profound in high risk women, these women are the one targeted by this study. Additionally, these women, often with a history of severe adverse pregnancy outcome, are particularly in need of treatment options. Since there are still low risk women to be included in the study, reported evidence for these women, will still be representative for a general population of pregnant women.

For obstetricians worldwide the management of FGR is still lacking therapeutic options. During the past decade therapeutic agents with possible perfusion optimizing potential have been evaluated in clinical trials.

Antiplatelet agents, like aspirin have been extensively investigated for prevention of preeclampsia and also FGR. A meta-analysis summarizing individual patient data of more than 32.000 women in 31 randomized trials showed a reduction in the relative risk of birth before 34 weeks’ gestation and of preeclampsia, but not of perinatal death or FGR [20]. Recently data from the ASPRE trial where the effect of 150 mg aspirin to prevent preeclampsia in high risk women was investigated also showed a reduction of FGR cases in women developing preeclampsia [21, 22] when started before 16 weeks of gestation [23].

Sildenafil citrate, a phosphodiesterase-5 (PDE-5) inhibitor preventing the degradation of the second messenger cyclic guanosine 3 ′,5 ′ -monophosphate by the enzyme PDE-5, is a potent vasodilator and has been proposed for the treatment of FGR pregnancies [24–26]. First results of an international randomized controlled trial, including women with diagnosis of FGR beyond 26 weeks of gestation (STRIDER trial) has so far failed to show therapeutic effects [27].

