To prove the effects of PETN on adverse pregnancy outcome, particularly the significant decrease in the incidence of FGR and preterm birth, as well as to confirm the the efficacy and safety of PETN, a randomized, double-blinded, placebo-controlled, multi-center trial was initiated.

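### Exploratory treatment comparisons in subgroups by time of delivery condition on a post-randomisation outcome and are open to selection bias if PETN shifts delivery time

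*Protocol article*

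**What the plan says.** After setting out the confirmatory test, the secondary analyses and a mixed-model sensitivity analysis, the Statistical analysis section of the protocol article adds: "Explorative analyses of endpoints will be additionally performed for subgroups according to time of delivery and maternal age". It gives no delivery-time cut-offs and no caution on interpretation. It plans no multiplicity adjustment and sets every test at 0.05.

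Four other places bear on the point:

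- **Timing of randomisation and treatment.** Inclusion criteria admit a "singleton pregnancy at 19^0^ to 22^6^ weeks of gestation who are over 18 years old and provide informed consent". Under Experimental and control interventions: "Following randomisation, oral intake of PETN or placebo two times daily will be continued until 36^6^ weeks".
- **Delivery time as an endpoint.** Primary outcome measures lists among the secondary endpoints "development of FGR requiring delivery before 30 and before 34 weeks` gestation" and "spontaneous preterm delivery before 34 weeks and before 37 weeks gestation".
- **Expected effect on delivery time.** The Discussion describes what the trial is to prove as "particularly the significant decrease in the incidence of FGR and preterm birth", and says that "the additional decrease in the rates of prematurity and perinatal death will be of tremendous benefit for the affected women".
- **Link to FGR.** The Discussion says that prematurity often accompanies FGR, because a fetus threatened by asphyxia or death has to be delivered early.

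**The concern.** A subgroup treatment comparison keeps the protection of randomisation only if membership is fixed before treatment or cannot be affected by it. Time of delivery meets neither condition. If PETN prolongs some pregnancies, the women on PETN who still deliver early are, on average, the more severe cases. Those who have moved into a later band are more severe than the placebo women already in it. Each band then compares unlike groups.

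At stake is the reading of the exploratory results. A drug without effect on FGR could look mildly harmful in every delivery-time band, and a real benefit could look smaller than it is. Such a subgroup also cannot guide treatment, because delivery time is unknown when treatment starts.

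**Working it through.** **1. The plan's own figure, and whether it depends on this point.** Inputs from the sample size section: placebo risks 0.42 (low risk) and 0.69 (high risk), low:high ratio 2:1, odds ratio 0.5, two-sided alpha 0.05, power 80%. A 1:1 allocation is assumed.

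- PETN risk = OR·p / (1 − p + OR·p). Low risk: 0.21/0.79 = 0.266. High risk: 0.345/0.655 = 0.527.
- N = [(1.960·√V0 + 0.842·√V1) / D]², with stratum weights w = 2/3 and 1/3.
- D = Σw(p1 − p2)/4 = 0.0393.
- V0 = Σw·p̄(1 − p̄)/4 = 0.0574.
- V1 = Σw[p1(1 − p1) + p2(1 − p2)]/8 = 0.0559.
- N = (0.6685/0.0393)² ≈ 289.3, rounded up to the stated 290.

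Delivery time appears nowhere in this calculation, so neither the confirmatory test nor its sample size is touched.

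**2. Are the conditions for selection bias present in the document?**

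| Condition | What the article says |
|---|---|
| Subgroup variable arises after randomisation | Randomised at 19+0 to 22+6 weeks and treated up to 36+6 weeks; delivery comes later |
| Treatment may change it | Fewer preterm births are an expected effect, and preterm delivery is a secondary endpoint |
| It shares causes with the endpoint | Prematurity and FGR are described as associated |

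The first and third are stated as fact. The second is an expectation, so the bias is conditional on it.

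**3. Endpoints defined by delivery time.** This needs no model. In a subgroup lying wholly at or beyond 37 weeks, spontaneous preterm delivery before 34 or 37 weeks has no events in either arm by construction. The same holds for FGR requiring delivery before 30 or 34 weeks in any subgroup wholly beyond those limits.

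**4. Illustrative size.** The article gives no figure for an effect on delivery time, so everything below except the first two items is an assumption.

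- Control risk: (2·0.42 + 0.69)/3 = 0.51.
- Overall relative risk (RR) under the design effect: PETN risk (2·0.266 + 0.527)/3 = 0.353, and 0.353/0.51 = 0.69.
- Latent severity S is standard normal. Birth-weight z = −0.7·S + √(1 − 0.49)·e. FGR means z below the cut-off giving a control risk of 0.51. PETN shifts z so that the overall RR is 1.00 or 0.69.
- Gestation at delivery = 38 − 1.6·S + 2·e′ + d weeks, where d is the delay in the PETN arm.
- Bands: under 34, 34 to under 37, and 37 weeks or more.

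| Overall RR | Delay d (weeks) | RR <34 | RR 34 to <37 | RR ≥37 |
|---|---|---|---|---|
| 1.00 | 0 | 1.00 | 1.00 | 1.00 |
| 1.00 | 0.3 | about 1.02 | 1.03 | 1.03 |
| 1.00 | 1 | about 1.05 | 1.09 | 1.09 |
| 0.69 | 0 | 0.84 | 0.74 | 0.62 |
| 0.69 | 1 | about 0.91 | 0.84 | 0.70 |

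The <34 band is the smallest, and its values vary by about 0.01 between runs. The proper comparator for the last row is the row above it, not 0.69. The shifts are 0.91 − 0.84 = 0.07, 0.84 − 0.74 = 0.10 and 0.70 − 0.62 = 0.08.

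**5. A second, simpler model.** Here one shared prognostic factor has a log-odds slope of 1.5 on both FGR and early delivery, control early delivery is 0.33, and PETN halves its odds. With no effect on FGR, the RR is 1.05 (early) and 1.07 (late). With an overall RR of 0.69, it moves from 0.77 to 0.82 (early) and from 0.63 to 0.69 (late). The direction is the same, with shifts of 0.05 to 0.06. With no effect on timing and none on FGR, both subgroup RRs return to about 1.00.

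**The case against.** The strongest reply is that little depends on these analyses. They are labelled exploratory and additional, and the primary test, the secondary analyses in the whole population and the sample size do not use them. The distortion needs PETN to change delivery time. A 1-week mean delay has no source in the article, and a 0.3-week delay gives only about 1.02 to 1.03 under the null. Showing outcomes by gestational age at birth is also legitimate as description.

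All of that stands and limits the size of the point. It does not remove it. The exploratory label warns of chance findings; selection bias is a different problem, which more patients would not reduce. The condition for the bias is also the article's own expectation.

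A reader might infer more than the document supports:

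- **That a subgroup RR of about 0.91 against an overall 0.69 is all bias, hiding a benefit in early deliveries.** Most of that gap is there without any effect on timing (0.84), because baseline risk is higher among early deliveries and the RR lies nearer 1. Moreover, 0.91 still favours PETN.
- **That delivery time is a step on the causal path to FGR.** The Discussion describes the reverse: early delivery is a response to a threatened fetus. The objection needs only a post-randomisation variable with shared causes.
- **That leaving the risk stratum out of the subgroup list is a defect**, given the remark that "the effectiveness of PETN to substantially improve pregnancy outcome has been especially profound in high risk women". The article already stratifies randomisation and the Mantel-Haenszel analyses by risk. Stratum-specific displays and homogeneity tests are details that an article may leave to the analysis plan.

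**Conclusion.** The point holds in conditional form. The plan names a post-randomisation variable as a subgroup for endpoint analyses. The article itself treats that variable as an outcome, expects PETN to change it and links it to FGR. If PETN shifts delivery time, the within-subgroup contrasts are subject to selection bias; if it does not, the distortion disappears in the models. It would be too strong to say that the contrasts are certainly biased.

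Under the assumptions shown, the effect is modest. Null RRs move up by about 0.02 to 0.09, and under a true overall RR of 0.69 the subgroup RRs move towards 1 by about 0.05 to 0.10. Direction and size depend on the assumed delay, the strength of the shared factor and the bands, none of which the article gives. That delivery-time endpoints are uninformative within delivery-time subgroups depends on no model. Maternal age remains a valid subgroup. This is a small point, but cheap to put right.

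**What to change.** In the Statistical analysis section, remove time of delivery as a subgroup variable for treatment contrasts. Alternatively, restrict it to a descriptive display of endpoints by gestational age at birth, without tests or treatment-effect estimates. Report time of delivery as an outcome by arm in all randomised women. Keep subgroup treatment contrasts to variables fixed at baseline, such as maternal age.

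This is a change of wording. It needs no new data, because gestational age at birth is already collected, and it leaves the confirmatory test and the 290/324 sample size as they are. All that is lost is an exploratory contrast that could not be interpreted as a treatment effect.

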## Discussion

FGR is the most important determinant of perinatal outcome in pregnancies with impaired utero-placental perfusion, at worst resulting in perinatal death. The relevance of reducing the occurrence, rate and extent of FGR is obvious in light of the associated outcomes. FGR neonates have an incredible risk to develop neonatal complications and lifelong health effects [2]. A reduction of this burden and the additional decrease in the rates of prematurity and perinatal death will be of tremendous benefit for the affected women. Furthermore, reduction of FGR and prematurity might additionally decrease the long-term consequences like development of diabetes and obesity in the affected children, thereby also contributing to relieve the general health system. The chosen composite endpoint represents the most severe outcome possible in growth restricted pregnancies and is justified by being the endpoint of our pilot study.

The management of FGR so far is driven by an approach to delay delivery, since prematurity is the most important determinant for perinatal outcome and lifelong health in growth restricted newborns. Nevertheless, in cases where intrauterine hypoxia is rising and intrauterine asphyxia and death is threatening, preterm delivery is required to save the baby’s life. Thus, prematurity is often associated with FGR, thereby deteriorating the infants long-term prognosis. The clinical parameters accepted to determine long-term clinical outcome of preterm children are the occurrence and severity of intracerebral bleeding, severe bowel affection (necrotized enterocolitis) and the long-time lung function which is determined by the fetal respiratory distress syndrome [17–19]. Therefore, preterm birth and very early preterm delivery, as well as perinatal outcome data was chosen as secondary endpoints.

Eligible patients for the proposed trial are pregnant women recognized to be at risk of adverse pregnancy outcome associated with FGR at mid gestation by impaired uterine perfusion. In the absence of a general screening for placentation failure by Doppler measurement at mid gestation in all pregnant women, those recognized with impaired placental perfusion are more likely to present with additional risk factors and do not represent the general population. However, since the effectiveness of PETN to substantially improve pregnancy outcome has been especially profound in high risk women, these women are the one targeted by this study. Additionally, these women, often with a history of severe adverse pregnancy outcome, are particularly in need of treatment options. Since there are still low risk women to be included in the study, reported evidence for these women, will still be representative for a general population of pregnant women.

For obstetricians worldwide the management of FGR is still lacking therapeutic options. During the past decade therapeutic agents with possible perfusion optimizing potential have been evaluated in clinical trials.

Antiplatelet agents, like aspirin have been extensively investigated for prevention of preeclampsia and also FGR. A meta-analysis summarizing individual patient data of more than 32.000 women in 31 randomized trials showed a reduction in the relative risk of birth before 34 weeks’ gestation and of preeclampsia, but not of perinatal death or FGR [20]. Recently data from the ASPRE trial where the effect of 150 mg aspirin to prevent preeclampsia in high risk women was investigated also showed a reduction of FGR cases in women developing preeclampsia [21, 22] when started before 16 weeks of gestation [23].

Sildenafil citrate, a phosphodiesterase-5 (PDE-5) inhibitor preventing the degradation of the second messenger cyclic guanosine 3 ′,5 ′ -monophosphate by the enzyme PDE-5, is a potent vasodilator and has been proposed for the treatment of FGR pregnancies [24–26]. First results of an international randomized controlled trial, including women with diagnosis of FGR beyond 26 weeks of gestation (STRIDER trial) has so far failed to show therapeutic effects [27].

Lees and co-authors demonstrated the clinical effect of NO-donors in pregnant women at risk before [11]. In a randomized placebo-controlled blinded trial he demonstrated an increased likelihood for complication free pregnancy upon administration of glycerol trinitrate (GTN). Due to the small sample size the study, however, failed to demonstrate significant effects for the primary reduction in FGR, preterm delivery and PE. Furthermore, the development of nitrate tolerance was observed within a few days, could additionally limit the clinical effect [28].

Recently, the group of Valensise showed an improvement of maternal hemodynamics in complicated pregnancies when NO-donors were added to the initiated hypertensive therapy. The authors conclude that, as a consequence of changes in maternal hemodynamics, utero-placental perfusion is ameliorated and thus pregnancy outcome improved [29]. Complementary, it was shown by our group before, that NO-donors improve placental perfusion without affecting fetal circulation [30].

Valensise and colleagues studied the effect of the addition of NO-donors to antihypertensive therapy in pregnancy, showing significant enhancement of maternal hemodynamics and plasma volume expansion, faciliating prolongation of pregnancy. By enhancing materno-placental perfusion NO donors reduce pregnancy complications associated with impaired perfusion [29].

PETN, however, has notably peculiar features which differentiate it from all other organic nitrates, such as nitroglycerin, isosorbide-5-mononitrate, and isosorbide dinitrate. Upon treatment with PETN no develop a nitrate tolerance can be observed, probably due to its specific impact on intracellular signalling pathways [28, 31]. PETN increases the expression of the antioxidant genes HO-1 and ferritin heavychain (FeHc) in human endothelial cells. These increase in HO-1 and FeHc expression potentially impact on mitochondrial ROS production and the inhibition of mitochondrial aldehyde dehydrogenase activity and thus the avoidance of tolerance developement [28]. So far it remains speculative, whether reduced ROS production and enhanced HO-1 expression might also serve as a mechanism provoking improved endothelial cell function and thus vascular health.

To prove the effects of PETN on adverse pregnancy outcome, particularly the significant decrease in the incidence of FGR and preterm birth, as well as to confirm the the efficacy and safety of PETN, a randomized, double-blinded, placebo-controlled, multi-center trial was initiated.

